## 6.7 SAMPLE SIZE

The intention is to recruit 55 participants, allowing for a 20% drop-out rate. With 44 completers analysed there is a minimum of 90% power to detect a 1.5 µg/L effect on osteocalcin with a two-sided test at the 5% level of significance, assuming an estimate of the SD at a single timepoint of 3.0 (5). This assumes cautiously that the correlation between the repeated measurements within patients across the two periods is 0.5, whereas a previous crossover trial(6) showed a correlation of 0.8.

Following a pilot study to elucidate a reference range for osteocalcin in healthy volunteers and patients with AI, it has been shown that individuals can demonstrate reductions of up to 2.4 µg/L in the short

PRED-AID Study Statistical Analysis Plan (SAP)

term after changes in their steroid replacement regimen. It is anticipated that that larger changes in osteocalcin will be seen when patients continue on their new regimens for a longer duration.

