#### 9.6.4 INFECTION RATES AND SEVERITY

**Outcome definition:** Treatment arm difference in the frequency of infections from baseline to Day 120.

**Analysis:** The GNCQ is a validated questionnaire that records the frequency of 6 different type of infections in the last 6 months (upper respiratory tract, lower respiratory tract, gastroenteritis, mucosal infections, lower urinary tract infections and flu). Respondents record either 0, 1, 2, 3, >3, or unknown frequencies of each type of infection.

The data will be tabulated and reported for each infection type at baseline and Day 120 for each treatment arm. McNemar-Bowkers test will be used to assess the change between treatment periods.

The data will also be weighted as follows: 0 or "don't know" will be scored as 0.5, 1-2 as 2, 3 or more as 4. The sum of the weighted scores will be treated as a continuous variable and a multilevel repeated measures linear mixed effect model will be used to estimate the treatment arm difference, from baseline to Day 120. Similar to the primary analysis model, the model will include fixed effects for time (2 categories: Day 30 and Day 120), treatment arm (2 categories: prednisolone and hydrocortisone), period, type of AI (primary or secondary), baseline weighted GNCQ, use of a bone sparing agent. A random participant effect will be included and an unstructured covariance matrix will be used. The treatment effect at 120 days will be reported with a 95% confidence interval. The models assumptions about random effects distributions, correlation structure and residuals will all be investigated. If any assumptions are poorly met then log transformation of the analyte in question, will be explored. If the mixed effect model including both 30 and 120 day outcomes fails to converge, treatment effects will be estimated using separate mixed linear regression models for each follow-up time point.

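### The per-type infection test (McNemar-Bowker) ignores the ordering of the counts, is sparse with about 44 pairs, and has markedly less power than an ordered, period-adjusted comparison

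*Combined protocol and SAP*

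**What the plan says.** SAP 9.6.4 defines the infection outcome as "Treatment arm difference in the frequency of infections from baseline to Day 120". The source is the GNCQ, which "records the frequency of 6 different type of infections in the last 6 months", and "Respondents record either 0, 1, 2, 3, >3, or unknown frequencies of each type of infection".

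Two analyses follow.

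- **Per infection type.** "The data will be tabulated and reported for each infection type at baseline and Day 120 for each treatment arm", and then "McNemar-Bowkers test will be used to assess the change between treatment periods". No other test is planned for the individual types.
- **Overall.** The answers are weighted (zero or don't know is "scored as 0.5, 1-2 as 2, 3 or more as 4"). "The sum of the weighted scores will be treated as a continuous variable" in a linear mixed model with treatment, period, type of AI, baseline score and use of a bone sparing agent, and the Day 120 effect is reported with a 95% confidence interval.

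Section 9.6.4 does not say whether 'unknown' counts as a category in the Bowker table, whether levels are merged, how empty cells are handled, whether the p-value is exact or asymptotic, or whether the pairs are formed by drug or by period number. No infection rate, target difference or power is given for this outcome. The only power statement, in SAP 6.7, is for osteocalcin.

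**The concern.** A difference in frequency is a directional question about an ordered scale. Bowker's test asks something broader: whether every pair of mirror-image cells in the table is equal. A shift towards more infections on one drug is spread over 10 or 15 separate contrasts, and a move from 0 to >3 counts no more than a move from 0 to 1. With a few dozen pairs most of those contrasts hold nobody or one person, so the chi-square reference is poor.

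The test also leaves out features that the SAP asks for elsewhere. Section 6.9 wants analyses adjusted for type of AI (section 9.1 allows stated exceptions), and section 9.1 wants treatment effects reported with 95% confidence intervals. Bowker adjusts for neither period nor type of AI and yields no effect estimate.

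Infection rate and severity is a listed objective (protocol section 2), and the protocol expects equivalent outcomes on the two drugs (section 1.2). A set of non-significant per-type tests would say little about whether a given type of infection had become more common, yet could be taken as support for that expectation.

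**Working it through.** **Sample size carried over from the plan.** SAP 6.7 states: "With 44 completers analysed there is a minimum of 90% power to detect a 1.5" µg/L effect, with SD 3.0, correlation 0.5 and two-sided 5%. SD of the paired difference = 3.0 × √(2 × (1 − 0.5)) = 3.0. Standard error = 3.0/√44 = 0.452, and 1.5/0.452 = 3.317. Power = Φ(3.317 − 1.960) = 91.3% by normal approximation, or 90.0% by paired t. Recruitment is 44/(1 − 0.20) = 55. The plan's figures reproduce, and 44 is used below as the number of pairs.

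**What Bowker tests.** X² = Σ over i<j of (n_ij − n_ji)²/(n_ij + n_ji), with k(k − 1)/2 degrees of freedom. For k = 5 this is 5 × 4/2 = 10; with 'unknown' as a sixth level it is 6 × 5/2 = 15. Forty-four pairs over 25 cells average 44/25 = 1.8 per cell, and they crowd into the low counts. A pair of cells with no one in it contributes 0/0. Software may keep 10 df or count only non-empty pairs, so both are shown.

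**Assumptions (none is in the documents).** Counts per participant are Poisson with a gamma between-person factor of mean 1 and variance 0.5 or 1.0, capped at >3. There are no 'unknown' answers and no overlap of recall between drugs. Pairs are formed by drug, which is the favourable reading. The true rate is doubled on one drug. There were 1,500 to 4,000 simulated trials per setting; at 1,500 trials a power of 60% has a Monte Carlo standard error of √(0.6 × 0.4/1500) = 1.3 points.

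Power from one run of 1,500 trials per setting, 44 pairs, range over the two variances:

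| Mean per window | Bowker, 10 df | Bowker, non-empty df | Bowker, exact | Wilcoxon signed-rank |
|---|---|---|---|---|
| 0.1 vs 0.2 | 0% | 9-11% | 8-10% | 18-20% |
| 0.2 vs 0.4 | 0% | 9-14% | 15-20% | 36-38% |
| 0.4 vs 0.8 | 1% | 12-15% | 26-28% | 61-64% |
| 0.75 vs 1.5 | 7-12% | 19-27% | 40-49% | 84-87% |
| 1.0 vs 2.0 | 14-23% | 26-33% | 50-54% | 89-93% |

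A rank-sum test on period differences between sequences, which also removes the period effect, loses only a few points against the signed-rank test. Over all runs, signed-rank and rank-sum together give about 58-66% at 0.4 vs 0.8 and 78-86% at 0.7 vs 1.4. Bowker gives about 1% or 10-17% at 0.4 vs 0.8, and 6-10% or 17-24% at 0.7 vs 1.4 (10 df or non-empty df).

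**Sparseness and size.** With variance 1.0, the average number of non-empty pairs of cells out of 10 is 2.1 at mean 0.1, 5.9 at 0.4 and 8.1 at 0.75. With no true difference Bowker rejects 0-0.7% of the time (10 df) or about 1-5% (non-empty df), against about 4-6% for the ordered test.

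**Variants, lower mean 0.4-0.75.**

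- Sixth level with 5% 'unknown' (variance 1.0): Bowker (non-empty df) 6-13%, ordered 57-81%.
- Three merged levels (0, 1-2, 3 or more): Bowker 29-65%, including runs without between-person variation.
- 55 pairs: Bowker (non-empty df) 17-54%, ordered 72-96%, including runs without between-person variation.

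**Recall window.** Assume 183 days of recall, 120 days on drug, a 14-day washout, hydrocortisone as the baseline drug and a true doubling on prednisolone. The look-back at the end of period 2 then includes 183 − 120 − 14 = 49 days of period 1.

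- Hydrocortisone first: prednisolone rate (120 × 2 + 63)/183 = 1.66 against 1.00, an apparent ratio of 1.66.
- Prednisolone first: 1.66 against (120 + 14 + 49 × 2)/183 = 1.27, an apparent ratio of 1.31.

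At means 0.4-0.75 the ordered test falls to about 22-40% and Bowker (non-empty df) to about 3-5%.

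**The case against.** The strongest reply is that this is a valid if inefficient test in a supplementary table. The outcome as a whole is analysed on a quantitative scale by the mixed model of the weighted sum, with adjustment for period and baseline and with a confidence interval. That stands, and a reader who inferred that the infection objective has no ordered analysis would be wrong. It does not cover the individual types, however. If one type of six doubles and five do not change (equal rates assumed, paired t test of the 0.5/2/4 sum in place of the mixed model), power on the sum is only 16-24%.

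A second reply is that the percentages are not properties of this trial. That is also right. They depend on infection rates, between-person variation, a df convention and the handling of 'unknown', none of which the documents give. With lower means from 0.1 to 1.5, and including runs without between-person variation, Bowker ranges over 0-74% and the ordered test over 18-99%. Exact p-values or merged levels narrow the gap, but the SAP specifies neither. What did not change in any setting was the ranking.

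A third reply is that six-month recall over four-month periods dilutes any effect. It does, for both tests. A reader should not infer that changing the test alone would bring power to 60-85%.

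**Conclusion.** The point holds for the six per-type tests. McNemar-Bowker discards the ordering, makes no adjustment for period or type of AI, gives no estimate, and with about 44 pairs is usually conservative. Its power for a directional shift was below that of an ordered test in every setting tried, usually by a wide margin. The two illustrations (0.4 vs 0.8 and 0.7 vs 1.4) rest on assumed rates, on between-person variation, and on no 'unknown' answers and no recall overlap.

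Three limits apply. For rare types (means of 0.1-0.2) the ordered test is itself weak, at about 18-40%. For frequent types Bowker can exceed 25%. The recall mismatch is a separate weakness that this change does not cure. Neither the primary analysis nor the analysis of the weighted sum is affected.

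**What to change.** In SAP 9.6.4, replace the McNemar-Bowker sentence with an ordered, within-participant comparison of prednisolone with hydrocortisone for each infection type:

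- Code the Day 120 answers 0, 1, 2, 3, >3 as ordered. Take each participant's period 1 minus period 2 difference and compare it between the two sequences by a Wilcoxon rank-sum test stratified by type of AI.
- Report a Hodges-Lehmann estimate with a 95% confidence interval. The difference between sequences estimates twice the treatment effect, so halve it.
- As an alternative, fit a mixed ordinal logistic model with treatment, period and type of AI, if it converges.
- Treat 'unknown' as missing in this test and report how often it occurs.
- Label the six tests as secondary, with no multiplicity adjustment.
- Keep the descriptive table.

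No new data are needed. The cost is a few lines of SAP text and an estimate on a capped ordinal scale. With many tied answers the Hodges-Lehmann estimate can be zero even when the distributions differ, so it should be read beside the table.

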#### 9.6.5 IMMUNOLOGY PROFILES

**Outcome definition:** Treatment arm difference in i) total white cells, ii) neutrophils, iii) lymphocytes, iv) eosinophils, v) basophils, vi) natural killer cells (including subtypes), vii) monocytes (including subtypes) viii) soluble immunological analytes; from baseline to Day 120.

**Analysis:** A multilevel repeated measures linear mixed effect model will be used to estimate the treatment arm difference in the above immunological markers, from baseline to Day 120. Similar to the primary analysis model, the model will include fixed effects for time (2 categories: Day 30 and Day 120), treatment arm (2 categories: prednisolone and hydrocortisone), period, type of AI (primary or secondary), baseline weighted GNCQ, use of a bone sparing agent. A random participant effect will be included and an unstructured covariance matrix will be used. The treatment effect at 120 days will be reported with a 95% confidence interval. The models assumptions about random effects distributions, correlation structure and residuals will all be investigated. If any assumptions are poorly met then log transformation of the analyte in question, will be explored. If the mixed effect model

#### PRED-AID Study Statistical Analysis Plan (SAP)

including both 30 and 120 day outcomes fails to converge, treatment effects will be estimated using separate mixed linear regression models for each follow-up time point.

The soluble immunological markers and subtypes of natural killer cells and monocytes to be assessed have yet to be determined. They will very likely include but not be limited to CD56+/CD16+ NK cells, CD56+/CD16 NK cells, CD14+/CD16 monocytes, CD14+/CD16+ monocytes, CD14/CD16+ monocytes and soluble CD16 antigen. The other specific markers to be assessed will be decided upon by the CI during the course of the study and will be based upon up to date published evidence.

### 9.6.6 SAFETY

**Outcome definition:** Treatment arm difference in i) FBC, ii) renal profile, iii) LFTs, iv) CK, v) ACTH, vi) CBG, vii) Bicarbonate viii) number of reports of myopathic symptoms, or nausea; from baseline to Day 120.

**Analysis:** A multilevel repeated measures linear mixed effect model will be used to estimate the treatment arm difference in the above safety outcomes (except (viii)), from baseline to Day 120. Similar to the primary analysis model, the model will include fixed effects for time (2 categories: Day 30 and Day 120), treatment arm (2 categories: prednisolone and hydrocortisone), period, type of AI (primary or secondary), baseline outcome. A random participant effect will be included and an unstructured covariance matrix will be used. The treatment effect at 120 days will be reported as a p-value with a 95% confidence interval. The models assumptions about random effects distributions, correlation structure and residuals will all be investigated. If any assumptions are poorly met then log transformation of the analyte in question, will be explored. If the mixed effect model including both 30 and 120 day outcomes fails to converge, treatment effects will be estimated using separate mixed linear regression models for each follow-up time point.

Data for symptom reporting will tabulated according frequency of reported symptoms will be presented at baseline and Day 120 for each treatment arm. McNemar's test will be used to assess the change between time periods.

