As participants will be changing their steroid treatment as part of this study, there is a risk of undertreatment. This risk will be minimised as patients will be trialled on the new regimen if they have not previously received it before. Possible symptoms will include tiredness, dizziness, pre-syncope, syncope, palpitations, and abdominal pain. These will be detected through symptom reporting, which will take place during all visits and telephone consultations. Participants will also have a 24-hour emergency contact number for a study clinician which they will be instructed to call if they feel unwell.

At times of intercurrent illness, participants will be asked to double the tablets that they are taking. This is usual clinical practice and will be overseen by a study clinician, who will be available on a 24-hour emergency contact number. Specifically, participants will be asked to take an additional tablet from their morning bottle for the first double dose, before doubling the number of tablets that they usually take from each bottle thereafter. Therefore, instead of taking one tablet from the morning, noon and afternoon bottles, participants will take two from each bottle at the allocated time after the special arrangement for the first double dose.

The only procedure being undertaken as part of this study is venepuncture, thus there may be slight pain when this is performed. Efforts will be made to minimise the frequency and quantity of blood taken

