### 8.3 SAFETY VARIABLES

The safety variables measured in this study are included as part of the secondary efficacy variable and are reproduced below:

- Safety
  - assessed by reporting of symptoms of steroid deficiency and myopathy and review of routine monitoring blood tests including full blood count (FBC), renal profile, liver function tests (LFTs), creatine kinase (CK), Adrenocorticotrophic hormone (ACTH) cortisol binding globulin (CBG) and bicarbonate.

In addition, the number of adverse events (AE), serious adverse events (SAE), and SUSARs (suspected unexpected serious adverse reactions) will be recorded for each Study Period.

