#### 9.7 SAFETY ANALYSIS

A safety set (SS) population, consisting of all participants who received at least one dose of the assigned intervention, will be defined for describing adverse events in. Adverse events will be summarised by type (AE or SAE) and treatment arm in a given period. AEs will be tabulated by treatment group for both the number of events and the number of participants with the type of event in a given period. A listing will be produced detailing all Serious Adverse Events (SAEs). Only descriptive analysis of safety will be performed, no formal statistical testing is planned.

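### SAP 9.6.6 compares only muscle symptoms or nausea, at baseline and Day 120, which is narrower than the steroid-deficiency symptom outcome that SAP 8.3 defines

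*Combined protocol and SAP*

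**What the plan says.** Protocol 3.1, SAP 8.2 and SAP 8.3 describe the safety outcome in the same terms: it is "assessed by reporting of symptoms of steroid deficiency and myopathy", together with routine blood tests.

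Protocol 1.2 identifies undertreatment as a risk of changing steroid. It states: "Possible symptoms will include tiredness, dizziness, pre-syncope, syncope, palpitations, and abdominal pain". It adds that these are picked up by symptom reporting at every visit and every telephone call. Protocol 8 places the visits on Days 1, 30 and 120 of each period and the calls on Days 8, 15, 60 and 90. Day 1 is on usual therapy, and blinded drug starts on Day 2.

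SAP 9.6.6 lists the symptom endpoint as item viii: "number of reports of myopathic symptoms, or nausea; from baseline to Day 120". The mixed model, which has a Day 30 term, is for the "treatment arm difference in the above safety outcomes (except (viii)), from baseline to Day 120", so symptoms are left out of it. For symptoms the SAP says that the "frequency of reported symptoms will be presented at baseline and Day 120 for each treatment arm", and that "McNemar's test will be used to assess the change between time periods".

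SAP 8.3 then adds counts of AEs, SAEs and SUSARs on top of the symptom outcome. SAP 9.7 says: "Adverse events will be summarised by type (AE or SAE) and treatment arm in a given period". It also provides tables of events and of participants per type of event, a listing of SAEs, and no testing.

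**The concern.** The outcome that is defined and the outcome that is compared are not the same. The definition covers steroid deficiency, which is the risk the protocol attaches to switching drug. The comparison names muscle symptoms and one deficiency symptom, at a single on-drug time point nearly four months after the switch.

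A deficiency symptom that follows a switch could appear at the Day 8 or Day 15 call. By Day 120 it could have resolved, been covered by tablet doubling during illness (protocol 6.5), or ended in withdrawal. The trial could then report no difference in its symptom outcome without having compared the drugs on dizziness, syncope or palpitations. SAP 5.1 puts safety alongside efficacy in the primary objective, so readers will look at this comparison.

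**Working it through.** The plan states no figure for the symptom outcome. Its one design figure is for osteocalcin, and it reproduces. The SD of the within-patient difference is 3.0 × √(2 × (1 − 0.5)) = 3.0, and the SE is 3.0/√44 = 0.452. Power for 1.5 µg/L is 0.913 by the normal approximation and 0.900 by the t distribution, and 44/0.80 = 55. The present point does not depend on it; the rest is a comparison of sections.

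**Symptoms**
- Protocol 1.2 lists six. Item viii names 0 of 6.
- Protocol 1.1 adds lethargy, depression and nausea as signs of under-replacement. Item viii names 1 of 9 (nausea), or 1 of 8 if lethargy and tiredness are counted as one.

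**Contacts per period**
- After blinded drug starts on Day 2: Days 8, 15, 30, 60, 90 and 120, which is six.
- In the symptom comparison: data "presented at baseline and Day 120 for each treatment arm". Baseline is on usual therapy, so Day 120 is the only on-drug point: 1 of 6.
- In the first month (Days 8, 15, 30): 0 of 3.

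**Illustration only.** The documents give no onset or duration for such symptoms. Assume that onset is uniform over Days 2 to 30 (28 days) and that a symptom is counted only if present on the contact day.

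| Duration | Seen on Day 8, 15 or 30 | Seen on Day 120 |
|---|---|---|
| 7 days | (6 + 7 + 7)/28 = 71% | 0% |
| 14 days | (13 + 14)/28 = 96% | 0% |
| 28 days | 28/28 = 100% | 0% |

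The latest end date in the table is Day 30 + 28 = Day 58, hence the zeros. A symptom that persists to Day 120 would be seen there.

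**Pairing for McNemar's test.** The test needs two paired yes/no results per participant, and the SAP does not say which two. If they are baseline and Day 120 of the same period, there is a difficulty. Eligibility requires stable hydrocortisone or prednisolone, and Day 1 is taken on that usual drug. In one of each participant's two periods the pairing would therefore set a drug against itself. Only a pairing of prednisolone with hydrocortisone answers the trial's question.

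**Sensitivity of the test.** With all discordant pairs in one direction, the exact two-sided p-value is 2 × 0.5⁵ = 0.0625 for five pairs and 2 × 0.5⁶ = 0.031 for six. A rare symptom will seldom reach that, so the table by symptom matters at least as much as the test.

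**The case against.** The strongest reply is that early symptoms are reported elsewhere. Protocol 7.1 counts any unfavourable symptom as an adverse event, protocol 7.3 asks for all of them, and protocol Appendix 2 schedules AE reporting at every call and visit. Dizziness at the Day 8 call therefore enters the SAP 9.7 tables by treatment and period, and a serious syncope would be listed. This stands. It limits the gap to the symptom comparison, but does not close it. SAP 9.7 is descriptive, does not group deficiency symptoms, and glosses type as AE or SAE, so tabulation by symptom is possible but not stated. SAP 8.3 also presents AE counts as an addition to the symptom outcome. Protocol 7.3.2 exempts relapse of, and death from, adrenal insufficiency from SAE reporting, so the SAE listing may not cover the severe end.

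Other points stand in part:
- Nausea is a deficiency symptom under protocol 1.1, so the comparison is not empty of them.
- The protocol 1.2 list is worded as examples, not as an endpoint definition.
- The SF-36 energy/fatigue domain and the Addi-QoL are modelled at Days 30 and 120 (SAP 9.6.7). They may partly reflect tiredness, but do not count syncope, dizziness or palpitations.
- Participants new to the alternative drug have at least two weeks on it before randomisation, which lowers the early risk by an unstated amount.
- Item viii could be read as a count over the whole interval. The analysis sentence and the choice of McNemar's test both point to two time points instead.
- A single any-symptom outcome could let common tiredness swamp syncope. This is a fair warning about the remedy, and the fix below allows for it.

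**Conclusion.** The point holds as a mismatch between the defined and the compared outcome. Item viii names none of the six protocol 1.2 symptoms and one of the nine across protocol 1.1 and 1.2. It uses one of six on-drug contacts per period and none from the first month. These counts rest on reading the SAP 9.6.6 analysis sentence as fixing two time points; the interval-count reading would remove the timing part but not the narrowing of symptoms.

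Two stronger conclusions might be inferred, and the documents support neither. One is that the other five contacts are discarded and early undertreatment would go unreported; those reports still reach the AE tables. The other is that pooling nausea with muscle symptoms lets under- and over-replacement signals cancel; SAP 9.6.6 states no composite, and its wording is compatible with separate rows.

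This is one component of a secondary safety outcome. It does not affect the osteocalcin analysis, for which alone the trial is sized. It should be corrected before unblinding, but it does not put the trial's main conclusion at risk.

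**What to change.** Amend the SAP before any unblinded data are extracted.

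1. In 9.6.6, item viii, define two separate outcomes: steroid-deficiency symptoms (the protocol 1.1 and 1.2 lists, with nausea kept here) and myopathic symptoms.
2. For each, record whether the participant reported it at any on-drug contact in the period: Days 8, 15, 30, 60, 90 and 120.
3. Tabulate every symptom individually by the drug being taken, so that frequent tiredness does not hide a less frequent symptom such as syncope.
4. Compare prednisolone with hydrocortisone within participant, and state that this is the McNemar pairing.
5. In 9.7, state that AEs are tabulated by symptom or term, and reconcile the statement that safety is described without testing with the McNemar test in 9.6.6.

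The data are already due to be collected at each of these contacts, so no visit or procedure is added. The cost is SAP wording, a short coding list, and a few more rows in the safety table.
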